#### Comparator arm: continuous treatment (standard care)

Participants randomised to the comparator arm will continue risankizumab monotherapy at fixed 12-weekly intervals, as per standard care.

### Outcomes

#### Primary outcome

The primary outcome will be the practicality and acceptability of the two personalised biologic dose minimisation strategies, assessed as a composite measure comprising recruitment and retention rates, as well as adherence to and acceptability of the allocated treatment strategy (table 3).^31^

**Table 3 T3:** Components of the primary outcome

Component	Evaluation criteria
Recruitment rate	Proportion of eligible individuals invited to participate who are randomised.
Retention rate	Proportion of participants who complete the 12-month follow-up visit.
Adherence	Adherence to the allocated treatment strategy, assessed using patient and clinician questionnaires.
Acceptability	Acceptability of the allocated treatment strategy, using relevant constructs from the theoretical framework of acceptability.^31^ This will be assessed through patient and clinician questionnaires, with a subset of participants also taking part in one-to-one semistructured qualitative interviews.

These components will inform whether progression to a full-scale, definitive RCT is appropriate:

If all components exceed 80%, the study will proceed to a definitive RCT without protocol modifications.If any component falls between 20% and 80%, the study may still progress, but with protocol modifications.If any component is below 20%, progression to a full trial will be halted.

These progression criteria were developed through study team consensus and may be refined during the study with input from patients, clinicians and researchers, under the guidance of the trial steering committee (TSC).

#### Secondary outcomes

The secondary outcomes include:

Clinical and healthcare outcomes over the 12-month period, comparing the different groups based on the following:Number of weeks per patient spent with ‘disease control’. Disease control is defined as a Patient Global Assessment Score of clear or nearly clear skin with no evidence of disease worsening.Number of ‘disease worsening’ episodes per patient. Disease worsening is defined as an assessor blind increase in PASI of ≥3 from baseline with a minimum PASI of 5 (assessed via in-person visits), and/or a treatment change such as biologic dose escalation, biologic switch or the addition of adjunctive therapy. This definition has been previously used in RCTs of immune-mediated inflammatory diseases, including psoriasis.^32^Disease severity at the end of the trial, assessed through blinded PASI and Physician Global Assessment at the month 12 in-person visit.Patient-reported outcomes including the following:Dermatology Life Quality Index.EuroQol 5-Dimension 5-Level Questionnaire (EQ-5D-5L).Itch Numerical Rating Scale.Patient Health Questionnaire for depression.Generalised Anxiety Disorder questionnaire.Brief Illness Perception Questionnaire.Psoriatic Arthritis Impact of Disease Questionnaire, if participants have a rheumatologist confirmed diagnosis of psoriatic arthritis.Treatment and healthcare burden, assessed by total drug exposure, number of drug-free weeks per patient (post each 12-week cycle) and number of PIFU visits.Safety and tolerability, assessed by:Incidence of adverse events and serious infections.Incidence of new onset psoriatic arthritis (screened for using the Psoriasis Epidemiology Screening Tool) or flare of psoriatic arthritis (as confirmed by a rheumatologist).Proportion of patients with antidrug antibodies.Number of injection site reactions.Feasibility of collecting healthcare cost and resource use data for each treatment strategy assessed by the proportion of missing data.Acceptability and practicality of follow-up completion, measured by:Proportion of participants who complete the three-monthly self-assessments (including submission of photographs) using the mySkin app.Proportion of missing data per participant.Duration of in-person study visits at month 12 and during PIFU visits.Refine the model-informed precision dosing dashboard for TDM-guided biologic treatment using longitudinal PK and PD data, to enhance its future utility.^27^Acquisition of clinical samples and data for future use by the wider scientific community.Acceptability and practicality of self-taken blood samples for serum analysis, assessed by questionnaires evaluating relevant constructs from the theoretical framework of acceptability, proportion of participants who submit a self-taken blood sample following study team invitation, time from invitation to sample receipt by study team, proportion of self-taken samples from which the serum drug concentration is successfully measured and qualitative interviews with a subset of participants.^31^Acceptability and practicality of genotype testing, assessed by participant questionnaires evaluating relevant constructs from the theoretical framework of acceptability and qualitative interviews with a subset of participants.^31^

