Adherence and acceptability questionnaires					X		X	
Resource use			X	X	X	X	X	X
Nested qualitative study								
Semistructured interviews¶							X	

* Serum albumin, creatinine, C reactive protein, risankizumab concentration, anti-risankizumab antibody titre.

† Self-taken blood sample.

‡ Training provided on treatment strategy, PIFU and the mySkin app.

§ Assessor-blind skin assessments.

¶ Subset of participants and clinicians only.

BIPQ, Brief Illness Perception Questionnaire; DLQI, Dermatology Life Quality Index; EQ-5D-5L, EuroQol 5-Dimension 5-Level; GAD, Generalised Anxiety Disorder Questionnaire; NRS, Numerical Rating Scale; PASI, Psoriasis Area and Severity Index; PEST, Psoriasis Epidemiology Screening Tool; PHQ, Patient Health Questionnaire; PIFU, Patient-Initiated Follow-Up; PsAID, Psoriatic Arthritis Impact of Disease.

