#### Intervention arm 1: patient-led ‘as-needed’ treatment

Participants randomised to patient-led ‘as-needed’ treatment will pause risankizumab monotherapy and resume it at the first sign of self-assessed psoriasis recurrence to maintain clear or nearly clear skin, keeping a minimum dosing interval of 12 weeks^23^. Recurrence is defined as Patient Global Assessment Score of mild (ie, no longer clear/nearly clear).

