#### Intervention arm 2: TDM-guided treatment

For participants randomised to TDM-guided treatment, a clinician will use an online precision dosing dashboard incorporating a PK model for risankizumab therapy to calculate a personalised dosing interval, which will be applied throughout the 12-month study period.^27^ To generate this interval, the dashboard requires the serum concentration of risankizumab and the anti-risankizumab antibody titre, measured using routine rapid chemiluminescence assays following the screening visit. The dashboard also requires the date of the last risankizumab dose, body weight, PASI and the serum levels of albumin, creatinine and C reactive protein.

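### The antidrug-antibody proportion is compared between arms that differ by design in circulating drug; if the assay is drug-sensitive, the raw comparison leans against the reduced-exposure arms

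*Protocol article*

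**What the plan says.** Under Secondary outcomes, one of the safety and tolerability measures is "Proportion of patients with antidrug antibodies". It is a plain proportion, with no link to the drug level in the sample.

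The secondary outcomes open with clinical and healthcare outcomes, "comparing the different groups based on the following". Whatever level of that list the safety item belongs to, the Objectives section settles its use: safety and tolerability of each minimisation strategy are set against standard care, and these data are to supply effect sizes for planning a definitive trial.

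Drug exposure by arm, from the Interventions section:

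- As-needed arm: participants "will pause risankizumab monotherapy and resume it at the first sign of self-assessed psoriasis recurrence", "keeping a minimum dosing interval of 12 weeks".
- TDM-guided arm: a clinician uses the dashboard to "calculate a personalised dosing interval, which will be applied throughout the 12-month study period".
- Continuous arm: participants "will continue risankizumab monotherapy at fixed 12-weekly intervals".

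The TDM section says that the drug concentration and antibody titre needed by the dashboard are "measured using routine rapid chemiluminescence assays following the screening visit". Table 2 schedules blood at screening, month 6 (self-taken), month 12 and patient-initiated follow-up visits. Its footnote lists the analytes together: "Serum albumin, creatinine, C reactive protein, risankizumab concentration, anti-risankizumab antibody titre". Timing relative to the last dose is not given.

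**The concern.** In some assays, circulating drug binds antibody and turns a true positive into a negative. If this assay behaves that way, the chance of detecting an antibody depends on how much drug is in the tube, and that depends on the arm. An adherent continuous-arm participant is never sampled more than 12 weeks after a dose. An as-needed participant who has not recurred may be sampled much later.

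The bias would run in one direction, making the strategies under test look more immunogenic. A genuine rise in antibodies from pausing and restarting would look the same, so the plain proportion cannot tell the two apart. Immunogenicity is a natural safety question for intermittent dosing. A larger trial would not average out a systematic error of this kind, and the Objectives section intends these data to inform that trial.

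**Working it through.** **The plan's own precision.** No figure is stated for antibodies. Sample size gives about ±10% for overall retention and about ±20% for acceptability and adherence within an arm. The half-width 1.96 × √(p(1 − p)/n) at p = 0.5 gives 10.3 points for n = 90 and 17.9 points for n = 30, so both stated figures reproduce.

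**How far drug level could differ (assumed inputs).** The article gives no half-life. Assume 21 to 35 days and one-compartment decline. The level 26 weeks after a dose, relative to the 12-week trough, is exp(−k × 98 days) with k = ln 2 / half-life: 0.039, 0.088 and 0.144 for half-lives of 21, 28 and 35 days. A participant still off drug at 26 weeks would therefore carry about 4 to 14% of the continuous-arm trough. This shows that a contrast in drug level is plausible. It says nothing about how far detection falls.

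**Spurious difference (assumed inputs).** Prevalence and assay sensitivity are not in the article. Let true prevalence π be equal in all arms, detection complete in low-drug samples, and detection s in drug-rich samples. If all minimisation-arm samples are low-drug and all continuous-arm samples drug-rich, the difference is π × (1 − s):

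- π = 20%, s = 0.5: 0.20 × 0.5 = 10 points (3 of 30 participants).
- π = 20%, s = 0.9: 0.20 × 0.1 = 2 points (0.6 of 30).
- π = 30%: 15 to 3 points over the same range of s.

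These are upper bounds for the given inputs. If only a fraction f of minimisation-arm samples, and a fraction g of continuous-arm samples, are low-drug, the difference becomes π × (1 − s) × (f − g).

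**Sensitivity below 1 in low-drug samples.** The table gives the spurious difference in points, for sensitivity in drug-rich v low-drug samples. The last column is the 95% half-width for a difference with 30 per arm in the 0.5 v 0.9 case.

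| True prevalence | 0.9 v 0.9 | 0.7 v 0.9 | 0.5 v 0.9 | 0.3 v 0.9 | 95% half-width |
|---|---|---|---|---|---|
| 5% | 0 | 1 | 2 | 3 | 9.3 |
| 10% | 0 | 2 | 4 | 6 | 12.9 |
| 20% | 0 | 4 | 8 | 12 | 17.4 |
| 30% | 0 | 6 | 12 | 18 | 20.4 |

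The 0.5 v 0.9 case corresponds to an apparent ratio of 1.8.

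**Against sampling noise.** For the 10-point case (20% v 10%), the half-width is 1.96 × √((0.2 × 0.8 + 0.1 × 0.9)/30) = 17.9 points. For the 2-point case (20% v 18%), it is 1.96 × √((0.2 × 0.8 + 0.18 × 0.82)/30) = 19.8 points. The artefact lies inside the interval in both.

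**Number of samples.** Patient-initiated visits add blood samples. If antibody status were counted as ever positive, per-sample detection of 0.5 would find 50% of true positives with one sample and 1 − 0.5² = 75% with two independent samples. This favours a single fixed timepoint.

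**The case against.** The strongest reply is that the causal step is not in the article. It names a chemiluminescence assay and says nothing of drug interference, and it ties that assay to the screening sample used by the dashboard; the month-12 assay is not named. A reader might infer that detection is already confounded with arm. The documents do not support that as a fact. This stands, and the point must be conditional.

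Second, positivity rules, sampling windows and joint reading with drug level commonly sit in an analysis plan or laboratory manual, neither of which is shown. A reader might infer that the plan has decided to ignore drug level. It has not: nothing in the article excludes a joint reading, and both quantities are listed for the same sample. What remains is that the outcome, as worded and as used in the Objectives, is a raw proportion set against standard care.

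Third, the 10 to 2 points might be read as an expected size. It is an upper bound for its inputs. As-needed participants who recur are re-dosed and may have recent drug at month 12, the TDM intervals are not stated, and continuous-arm samples may fall at trough. Each shrinks the contrast.

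Fourth, a reader might infer that washout will produce a false rise from screening to month 12. The plan states a proportion, not a change, and does not fix the timing of the screening sample relative to dosing, so it cannot be called drug-rich.

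Last, the trial is unpowered, plans no hypothesis tests, and leaves antibodies out of the progression criteria. That stands and limits the severity.

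**Conclusion.** The point holds conditionally and is minor. The outcome is a plain proportion, its between-strategy use is stated, and exposure differs by design. If the assay loses sensitivity in the presence of drug, the comparison is biased against the reduced-exposure arms, mainly the as-needed arm, and the raw figures cannot distinguish that from a true effect of intermittent dosing.

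The size rests wholly on assumed prevalence and detection. It is zero with a drug-tolerant assay and would exceed the 10-point bound only with higher prevalence or stronger interference than the central assumption. At 30 per arm it would usually be lost in sampling noise. No stated progression decision turns on it. The practical risk is that a raw difference is taken into the definitive trial as a safety signal or an effect size.

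**What to change.** Report month-12 antibody status by arm beside the risankizumab concentration in the same sample. Show participants who were already positive at screening separately, and state the assay's drug tolerance. Where a tolerance level is available, classify results as positive, negative with drug at or below that level, or inconclusive (negative with drug above it). Add a sentence that the raw between-arm proportion is not to be read as a strategy effect or used as an effect size for the definitive trial. If the analysis plan or laboratory manual already does this, a cross-reference is enough.

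The cost is one table and some wording, plus obtaining the tolerance figure from the laboratory or manufacturer. No new samples, visits or treatment changes are needed. The downside is that some negatives, mostly in the continuous arm, become inconclusive, so fewer results support a firm negative.

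### The bare count of injection site reactions cannot separate tolerability per dose from the number of doses; a per-injection rate should be reported beside it

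*Protocol article*

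**What the plan says.** Under Secondary outcomes, the protocol article gives four safety and tolerability items. They are "Incidence of adverse events and serious infections", new or flaring psoriatic arthritis, "Proportion of patients with antidrug antibodies", and "Number of injection site reactions". The clinical and healthcare outcomes are introduced as "comparing the different groups based on the following", and the secondary objectives ask for preliminary tolerability data on each strategy against standard care. No unit is attached to the reaction count, whereas some neighbouring outcomes are expressed per patient or as a proportion of patients.

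The number of injections depends on the strategy. Comparator participants "will continue risankizumab monotherapy at fixed 12-weekly intervals". As-needed participants "will pause risankizumab monotherapy and resume it at the first sign of self-assessed psoriasis recurrence", "keeping a minimum dosing interval of 12 weeks". In the TDM-guided arm the interval is set individually from a pharmacokinetic model, and the article gives no range for it.

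The article also provides for an injection log in the app (Interventions; Table 2 schedules it at training, at each three-monthly timepoint and at patient-initiated visits). Total drug exposure is a separate secondary outcome.

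**The concern.** The expected number of reactions in an arm is the number of injections multiplied by the risk per injection. The minimum interval means that as-needed dosing can match the comparator's frequency but not exceed it, so any difference in injection numbers pulls that arm's raw count down. A lower count could mean that each injection was tolerated equally well, better, or even somewhat worse.

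This matters because the as-needed strategy pauses and restarts the drug, and the article itself says that its safety in real-world settings is untested. How a dose is tolerated after a longer gap is a fair question for the definitive trial. The named measure cannot answer it without a denominator, while reduced drug exposure is already covered by other outcomes.

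**Working it through.** The article states no figure for injection site reactions, so there is none to reproduce. The check asks how far the risk per injection could rise before the raw count showed it.

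**Inputs from the protocol article**
- Comparator interval: 12 weeks (Comparator arm).
- As-needed interval: at least 12 weeks (Intervention arm 1).
- 30 participants per arm (Sample size).
- Median time to relapse after stopping a biologic: 12 to 34 weeks across studies, longer for IL-23 inhibitors (Background and rationale).

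**Assumptions**
- Time since the last dose at randomisation, U, is uniform over 0 to 12 weeks.
- Each as-needed participant recurs at the same fixed interval after every dose, set at 12, 20 or 34 weeks.
- The window is 52 weeks.

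**Expected injections per participant**
- Comparator: 52/12 = 4.33.
- 34-week interval: the first dose falls at weeks 22 to 34 and the second at weeks 56 to 68, outside the window. Expected 1.0.
- 20-week interval: the first two doses fall at weeks 8 to 20 and 28 to 40. The third falls at week 60 − U, inside the window when U ≥ 8, which has probability 4/12 = 0.33. Expected 2 + 0.33 = 2.33.
- 12-week interval: the same as the comparator, 4.33.

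**Break-even risk ratio per injection** = comparator injections / as-needed injections

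| Assumed interval | Injections | Break-even ratio |
|---|---|---|
| 12 weeks | 4.33 | 4.33/4.33 = 1.0 |
| 20 weeks | 2.33 | 4.33/2.33 = 1.9 |
| 34 weeks | 1.0 | 4.33/1.0 = 4.3 |

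Below the break-even ratio, the as-needed arm is expected to show fewer reactions than the comparator even though each injection carries more risk.

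**Illustration at arm level** (the mean of 2 doses and the 5% comparator risk are assumptions)
- Comparator: 30 × 4.33 = 130 injections; 130 × 0.05 = 6.5 expected reactions.
- As-needed: 30 × 2 = 60 injections. With the risk doubled to 10%, 60 × 0.10 = 6.0 expected reactions.
- The raw counts look alike (6.5 against 6.0), while the rates are 5% and 10%.
- Treating the counts as Poisson, the as-needed count is no higher than the comparator count with probability 0.61.

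**Precision of the per-injection ratio in that example**
- SE of the log ratio = √(1/6.5 + 1/6.0) = 0.566.
- 95% factor = exp(1.96 × 0.566) = 3.03.
- Interval for a true ratio of 2: 2/3.03 to 2 × 3.03, or about 0.66 to 6.1.
- With comparator risks of 2% and 10%, the interval is about 0.35 to 11.6 and 0.91 to 4.4.

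**The case against.** The strongest reply is that the count is legitimate as it stands. The trial compares strategies by intention to treat, and the number of reactions a participant has in 12 months under a strategy is the randomised comparison. Fewer reactions because of fewer injections is a real benefit. A per-injection rate conditions on dosing after randomisation, since further as-needed injections come from participants who recur, so it is not a clean randomised contrast. This stands, and it is why the rate should be added to the count and should not replace it.

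Second, a condensed article need not give denominators, and the analysis plan, which is not shown, may add them. The article does not say that the count will be left unadjusted. This keeps the point minor. It does not remove it, because the article does name the measure, and that measure mixes two quantities.

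Third, the size is assumption-driven. The relapse definition behind the quoted medians is not given, 34 weeks is the upper end, and the as-needed arm resumes treatment already at a mild Patient Global Assessment. At 12 weeks nothing is masked, and for the TDM-guided arm no size can be given. All of this stands.

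A reader might infer that tolerability as a whole rests on this count, that a raised risk would be hidden, or that the trial would give false reassurance. The article does not support these readings. The count is one of four items, antidrug antibodies are reported as a proportion of patients, and the injection log and total drug exposure already supply a denominator. Nothing in the article shows that risk per dose rises on re-treatment. The trial does no hypothesis testing, and reactions are not among the progression criteria.

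**Conclusion.** The point holds as a minor improvement. The count is valid for reaction burden under each strategy, but alone it cannot distinguish tolerability per dose from the number of doses. If as-needed intervals averaged 20 to 34 weeks, the risk per injection could rise about 1.9- to 4.3-fold before the raw count equalled the comparator's; at 12 weeks the figure is 1.0 and there is no masking. These figures rest on a fixed common interval and a uniform time since last dose at randomisation. The added rate would make the quantity visible but would not settle it, given the wide intervals at this sample size.

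**What to change.** Keep the count per participant over 12 months, by arm, as the intention-to-treat measure. Beside it, report reactions per injection given, by arm, with a confidence interval, taking the number of injections from the injection log. Label the rate descriptive, and state that it is imprecise and conditions on dosing after randomisation.

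The cost is one line of outcome wording and one table row, and the denominator is already collected. A breakdown by time since the previous dose should be left out unless reactions are already recorded with dates. The article does not say that they are, so linking each reaction to a logged injection could need a change to the forms, and the events would be too few to split usefully.

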
#### Adverse events

Adverse event data will be collected during in-person study visits and through self-reported questionnaires embedded within the mySkin app. Expected events of special interest will be captured using follow-up self-report questionnaires, including (1) worsening of psoriasis and (2) worsening or emergence of psoriatic arthritis. These events will be reported as trial outcomes rather than adverse events.

